##### Secondary analysis

Standardised cognitive scores will also be compared between the two intervention groups using linear mixed effects regression, with partial clustering for multiple births, adjusted for socioeconomic status, parental risk index, sex, birth weight z-score, prematurity strata, antenatal and postnatal steroid use, multiple birth, key neonatal morbidity count and site. Missing data will be imputed or substituted as detailed for the primary estimand.

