#### Inclusion criteria (all must be satisfied)

born at <32 weeks PMA by best obstetric estimate (inborn or outborn).initial care is at a perinatal centre where routine care does not include formal environmental light/noise cycling.informed parental consent to trial participation, obtained either prior to or after birth (<168 hours for infants <28 weeks PMA, or <72 hours for infants ≥28 weeks PMA and <32 weeks PMA).

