#### Secondary outcomes

##### In hospital secondary outcomes

Survival to 36 weeks PMA.Indices of growth: weight, length, head circumference, body mass index z scores and growth velocity (also measured at 2, 6 and 12 months cPNA).Duration of hospitalisation to discharge from tertiary hospital and to discharge home.Indicators of respiratory illness includingIncidence of bronchopulmonary dysplasia (BPD) (defined by Jensen *et al*).^32^Severity of BPD (as defined by Jensen *et al* and right shift of the SpO_2_/P_I_O_2_ curve at 36 weeks PMA).^32
33^Requirement for respiratory support as determined by duration of mechanical ventilation, duration of any respiratory support and days of supplemental oxygen.Necrotising enterocolitis (NEC) Stage II or greater according to modified Bell’s Criteria.^34^Severe retinopathy of prematurity (ROP) stage III or more, or ROP Stage II plus as defined in the International Classification of ROP 3.^35^Neurologic injury as defined byGrade 3 or 4 intraventricular haemorrhage (IVH).^36^Presence of periventricular leukomalacia.Number of confirmed blood culture positive episodes of sepsis.

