### Randomisation

#### Sequence generation

Computer-generated randomisation tables were developed and uploaded by the study biostatistician ([name]) from The Kids Research Institute Australia (The Kids), Perth Australia. Treatment allocations were generated using random permuted block sizes, stratified by study centre and gestational age (<28 weeks’ PMA vs 28.0 to <32.0 weeks’ gestation), maintaining 1:1 randomisation of infants to each study group.

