### Statistical methods

#### Statistical methods for primary and secondary outcomes

A separate detailed SAP for the core CIRCA DIEM study outcomes will be produced by a blinded trial statistician and finalised prior to completion of the recruitment phase. Additional SAPs may be published ahead of database lock for the analyses of CIRCA DIEM substudies. Reported results will be in accordance with Consolidated Standards of Reporting Trials (CONSORT) guidelines. Estimands will be constructed for all outcomes and detailed in the SAP. In brief, continuous outcomes will be analysed using either the Wilcoxon-Mann-Whitney test or linear mixed effects regression, binary outcomes using logistic regression and time-to-event outcomes using proportional hazards models, adjusting for the covariates listed above. The false discovery rate employed for all secondary analyses will use the Benjamini-Hochberg algorithm.

After the final database lock, data will be analysed in R Statistical Programming software^44^ using the principle of intention to treat by the blinded trial biostatistician ([name]). Comparability of study groups at baseline will be based on summaries of participant demographic data. Descriptive statistics will include mean (SD), median (IQR) for continuous variables with symmetric and asymmetric distributions, respectively, and counts/percentages for categorical variables.

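### The adjusted cognitive-score model uses gestation only as a two-level stratum, leaving within-stratum gestation unused at a small cost in precision (minor)

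*Protocol article*

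**What the plan says.** The Secondary analysis section gives an explicit covariate list for the linear mixed model of the cognitive score. Besides socioeconomic status and a parental risk index, it names "sex, birth weight z-score, prematurity strata, antenatal and postnatal steroid use, multiple birth", and it ends with "multiple birth, key neonatal morbidity count and site". Gestation appears only through the prematurity strata, and birth weight only as a z-score whose reference is not named.

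The strata are defined under Sequence generation, where allocation is "stratified by study centre and gestational age (<28 weeks’ PMA vs 28.0 to <32.0 weeks’ gestation". That gives two levels. The first inclusion criterion is "born at <32 weeks PMA by best obstetric estimate", so gestation must be established for every infant before randomisation, both for eligibility and to assign the stratum.

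The Primary analysis section specifies an unadjusted Wilcoxon-Mann-Whitney test with deaths scored 55. For the other outcomes, Statistical methods for primary and secondary outcomes says "binary outcomes using logistic regression and time-to-event outcomes using proportional hazards models, adjusting for the covariates listed above". No covariate list precedes that sentence; the only one in the article follows it, under Secondary analysis.

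**The concern.** A two-level split treats gestation as constant across the five or so weeks below 28 and across the four weeks from 28 to 31. If the cognitive score depends on gestation within those bands, the part that the stratum misses goes into the residual unless another covariate carries it. A z-score for birth weight is normally constructed to be free of gestation, so it cannot do so.

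Gestational age is a baseline variable, cannot be affected by the intervention and is already known. Leaving it out makes the interval for the adjusted comparison somewhat wider than it need be and leaves chance imbalance in weeks within a stratum uncorrected. If the same list governs the models for survival, bronchopulmonary dysplasia and severe retinopathy, which can be expected to follow gestation closely, the cost there could be larger.

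**Working it through.** **The plan's own figure.** Inputs from Sample size: difference 4, SD 15, power 90%. Two-sided alpha of 0.05 is assumed from the 95% CI.
- Two-sample normal formula: 2 × (15 × (1.960 + 1.282) / 4)² = 295.5, so 296 per arm.
- Dividing 295.5 by the Wilcoxon relative efficiency 3/π = 0.955 gives 309.5, so 310 per arm against 312 stated. Power at 312 per arm is 0.902.
- Inflation: 624 / 0.9 / 0.8 = 866.7, against 868 stated.

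The sample size reproduces without any covariate, so nothing below alters it.

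**How much gestation the split leaves out.** The article gives no distribution of gestation. Assume it is uniform on 23-28 and 28-32 weeks, with 40% of infants below 28.
- Within-stratum variances: 25/12 = 2.08 and 16/12 = 1.33 weeks² (SD 1.44 and 1.15 weeks).
- Weighted: 0.4 × 2.08 + 0.6 × 1.33 = 1.63 weeks².
- Between strata: 0.4 × 0.6 × (30 − 25.5)² = 4.86 weeks².
- Share of a linear gestation signal kept by the split: 4.86 / (4.86 + 1.63) = 75%. About a quarter is left over (25-27% when 30-50% of infants are below 28 weeks).

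**Cognitive score, before other covariates absorb any of it.** Share of variance = slope² × within-stratum variance / 15².
- 1 point per week: 1.63 / 225 = 0.7%.
- 2 points per week: 6.53 / 225 = 2.9%.
- 3 points per week: 14.7 / 225 = 6.5%.

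With 30-60% of infants below 28 weeks, and gestation either uniform or skewed to older weeks, the ranges are 0.5-0.8%, 1.8-3.2% and 4.2-7.1%. For scale, the power of a plain two-sample comparison at 312 per arm moves from 0.915 to 0.916-0.933.

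**With the gestation-related covariates in the model.** Least squares was simulated 400 times per setting. Settings: 624 infants, 40% below 28 weeks, gestation skewed to older weeks within strata, 4-point effect, residual SD 13.5. Morbidity count was Poisson with log rate falling 0.22 per week and cost 2 points per morbidity. The log odds of postnatal steroid use fell 0.9 per week. In the runs with deaths, the log odds of death fell 0.65 per week and deaths scored 55. Clustering, site and the remaining covariates were left out. The table shows the fall in variance of the treatment estimate when weeks are added.

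| Slope (points/week) | No deaths, stratum only | No deaths, plus morbidity and steroids | Deaths at 55, stratum only | Deaths at 55, plus morbidity and steroids |
|---|---|---|---|---|
| 0.5 | 0.2% | 0.0% | 1.2% | 0.6% |
| 1 | 0.7% | 0.3% | 2.1% | 1.2% |
| 1.5 | 1.6% | 1.0% | 3.2% | 2.1% |
| 2 | 2.9% | 2.0% | 4.3% | 3.0% |
| 2.5 | 4.1% | 2.9% | 5.8% | 4.1% |

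The largest value for the fuller model, 4.1%, lowers the standard error from 1.151 to 1.127, about 2%. It is worth about 0.041 × 624 ≈ 26 infants. A second simulation with other assumed gestation links, at 1-2 points per week, agrees: adding the two covariates cut the gain from 1.6-4.9% to 0.5-2.3% with no deaths, and from 3.0-6.2% to 1.3-3.5% with 6% deaths.

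**Other outcomes, only if the same list applies.**
- *Length of stay*, assuming linear regression, 7 days per week and equal strata (within-stratum variance (2.08 + 1.33)/2 ≈ 1.7): unexplained variance is 49 × 1.7 ≈ 83 days². The ratio of stratum-only to weeks-adjusted variance is 1 + 83/14² = 1.42, 1 + 83/21² = 1.19 and 1 + 83/28² = 1.11 for residual SDs of 14, 21 and 28 days. With morbidity count and steroids in the model, the first two fall to 1.33 and 1.15.
- *Binary outcome* near 25%, odds ratio 0.65, 694 infants: simulated power rose from 0.592 to 0.619, 0.561 to 0.591 and 0.493 to 0.545 in three settings. In a separate run the log odds ratio moved from −0.396 to −0.436 while its standard error rose from 0.199 to 0.209. The ratio to the standard error goes from 1.99 to 2.09, so the gain is in power for a conditional effect; the interval does not narrow.

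**The case against.** The strongest objection is size. The listed model is richer than stratum plus z-score: postnatal steroid use and morbidity count both plausibly track gestation. A reader might infer that infants of 23 and 27 weeks receive identical adjustment. That holds for the stratum term but not for the whole model, and the table shows the other covariates taking up part of the signal. This stands and is why the estimate is 0-4%. It does not remove the point, because both variables can arise after randomisation and are poor stand-ins for a clean baseline value.

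A reader might also infer harm to the main result. The documents do not support this. The primary test is unadjusted, randomisation is stratified on the same split, and simulated type I error was 0.049-0.053 with or without weeks.

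The length-of-stay figures are tempting to quote as the cost. "Duration of hospitalisation to discharge from tertiary hospital and to discharge home" is a listed outcome, but continuous outcomes may be analysed by Wilcoxon or mixed regression and time-to-event outcomes by proportional hazards, and the article does not say which applies here. Under Wilcoxon no covariate enters. Nor does it say that the separate cost-effectiveness analysis uses these covariates, so no claim about the net-savings estimate follows.

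Extending the list to the morbidity outcomes is itself an inference from a cross-reference with nothing above it. A list containing a morbidity count is also an awkward fit for morbidity outcomes.

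Finally, the full analysis plan is not shown and may refine the list. The point remains because the article states the list explicitly and fixes gestation in coarse form.

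**Conclusion.** The point holds as a minor efficiency matter for the adjusted cognitive-score model. Some prognostic information known at baseline for every infant is unused, at a cost of about 0-4% of the variance of the treatment estimate, or about 2% of its standard error at most. This rests on assumed slopes of 0.5-2.5 points per week, an assumed gestation mix and mortality pattern, and a z-score standardised for gestation in the usual way; the article supplies none of these figures. It concerns precision, not bias, and leaves the primary analysis and the sample size as they are.

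For survival, bronchopulmonary dysplasia, severe retinopathy and length of stay the gain may be larger, but only if the cross-reference means this list, if length of stay is modelled by regression, and if the assumed slopes are near the truth.

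**What to change.** Under Secondary analysis, keep the prematurity stratum and add gestational age at birth in weeks and days, either linear within stratum or as a spline with few knots, fixed before database lock. The cost is one or two degrees of freedom and no new data.

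State which list "adjusting for the covariates listed above" refers to. If it is this one, add the same term to the adjusted models for survival, bronchopulmonary dysplasia and severe retinopathy, and for length of stay if that is analysed by regression.

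This change concerns gestation only. It does not endorse the rest of the list: postnatal steroid use and morbidity count can arise after randomisation and need their own justification.

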### Relevant concomitant care permitted or prohibited during the trial

Eyemasks may be applied for 24 hours/day in both the intervention (active comparator) and routine care (placebo comparator) group during any period when the infant is receiving phototherapy, in accordance with standards of care. Similarly, earmuffs may be worn for 24 hours/day in infants during high-frequency ventilation where that approach is standard care in that environment. Infants may still participate in the routine practice of afternoon ‘quiet time’ if required. This practice allows the dimming of light for 1–2 hours in the afternoon but does not permit the use of cot-covers, eye-masks or earplugs during this period.

Caffeine therapy will be timed in both study groups to be given with the first morning medications at or as close as possible to 8:00. Postnatal steroid administration, when required, will be timed so that the evening dose is given no later than 18:00 and the morning dose no earlier than 6:00. All other postrandomisation management of study infants is at the discretion of the clinical team.

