##### Primary analysis

Standardised cognitive scores will be compared between the intervention and control group at 24 (20–36) months cPNA (primary outcome) using the Wilcoxon-Mann-Whitney test and summarised using the median of differences (Hodges-Lehmann estimator), with asymptotic 95% CI. The primary estimand will be detailed in the SAP, excluding non-randomised siblings from multiple births. In brief, missing primary outcome data due to death will be replaced with a score of 55 (corresponding to –3 SD), or with a score of 40 (–4 SD) in a sensitivity analysis. Missing data, including incomplete Bayley-4 scores, scores outside time window and those missing due to LTFU or withdrawal will be imputed (Amelia II R package) using prematurity strata and multiple birth as predictors.^46^ A separate estimand will be defined for the primary outcome excluding participants with all-cause missing data.

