#### Interim analyses

Interim analyses for safety and data completeness will be conducted after 25%, 50% and 75% of the target sample cohort are recruited and have reached 36 weeks PMA (timepoint for assessment of neonatal morbidities). A blinded interim analysis will be performed after 25% and 50% of the participants have reached the 2-year endpoint to assess the assumptions in the sample size calculation. The DSMC will make recommendations to the Trial Steering Committee regarding trial continuation after each interim safety and efficacy analysis. The Trial Steering Committee will make the final decisions about trial termination if required.

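### The secondary adjusted analysis of the cognitive score conditions on postnatal steroid use and a neonatal morbidity count, both determined mostly after randomisation

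*Protocol article*

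**What the plan says.** Under Secondary analysis, the protocol article plans a second comparison of the primary endpoint: "Standardised cognitive scores will also be compared between the two intervention groups using linear mixed effects regression". The adjustment set ends with "antenatal and postnatal steroid use, multiple birth, key neonatal morbidity count and site". No reason is given for including postnatal steroids or the morbidity count, the components of the count are not defined, and the model is not described as a mediation or direct-effect analysis.

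The primary analysis is separate and has no covariates. Scores are compared "using the Wilcoxon-Mann-Whitney test and summarised using the median of differences (Hodges-Lehmann estimator), with asymptotic 95% CI".

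For other outcomes, the Statistical methods section plans "binary outcomes using logistic regression and time-to-event outcomes using proportional hazards models, adjusting for the covariates listed above". No covariate list comes before that sentence. The only candidates earlier in the article are the two stratification factors, centre and gestational-age group, under Sequence generation. The only full list is the one under Secondary analysis, which comes later and is written for the cognitive score.

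**The concern.** Randomisation makes the arms comparable on what is fixed before allocation. A covariate that the intervention can alter lies on the pathway from assignment to outcome, and adjusting for it takes out some of the effect the trial sets out to measure. If unmeasured illness severity drives both the covariate and the outcome, adjustment also makes the arms differ in severity among infants with the same covariate value.

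The stake is the interpretation of the secondary result. This is the only covariate-adjusted analysis of the cognitive score that the article describes, and the only one said to model clustering of multiple births. Readers will use it to corroborate the primary result, and will not know that it may answer a different question.

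The unclear back-reference matters for a second reason. Under Trial status, in-hospital morbidity and mortality are to be published after the intervention phase, ahead of the primary result. Which covariates enter those models needs to be clear by then.

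**Working it through.** **1. The plan's own figures.** The sample size is for the Wilcoxon test, with a difference of 4 points, SD 15 and 90% power. Two-sided alpha of 0.05 is assumed; the article does not state it, but it fits the 95% CI.
- Normal formula: 2 × [15 × (1.960 + 1.282) / 4]² = 295.5 per arm.
- Divided by the Wilcoxon efficiency 3/π = 0.955: 309.5, so 310 per arm, against 312 stated.
- Simulated Wilcoxon power at 312 per arm (4,000 runs, normal data): 0.904.
- Inflation: 312 / 0.90 / 0.80 = 433.3, so 434 per arm and 868 in total, as stated.

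The figures reproduce. They rest on an unadjusted test, so nothing below changes them.

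**2. Timing of the two covariates.**
- Consent is limited to "<168 hours for infants <28 weeks PMA, or <72 hours for infants ≥28 weeks PMA and <32 weeks PMA" (Inclusion criteria), and the intervention then runs for weeks.
- Interim safety analyses wait until infants "have reached 36 weeks PMA (timepoint for assessment of neonatal morbidities" (Interim analyses). That is well after enrolment.
- Steroids are in-trial management: "Postnatal steroid administration, when required, will be timed so that the evening dose is given no later than 18:00" (Relevant concomitant care).
- Morbidities are outcomes. The in-hospital secondary list has, for example, "Necrotising enterocolitis (NEC) Stage II or greater according to modified Bell’s Criteria", along with BPD, severe ROP, IVH, periventricular leukomalacia and sepsis. A secondary hypothesis is that the intervention does not increase them.

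**3. Effect on the cognitive estimate.** If severity does not itself affect the score:

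adjusted estimate = total effect − (points per morbidity × change in mean count) − (points for steroid use × change in steroid risk).

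For example, with 3 points lost per morbidity and a count lower by 0.2, the morbidity part gives 4.0 − 3 × 0.2 = 3.4. The steroid part lowers this slightly, and simulation gives 3.34.

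All inputs here are assumptions, not figures from the documents: control mean of 0.9 morbidities; 3 or 6 points lost per morbidity; 3 points lost with steroid use; residual SD 12; odds of steroid use shifted by the same ratio as the count; an unmeasured severity factor driving morbidity and steroid use, with either no direct effect on the score or 4 points lost per SD. The total effect is fixed at 4.0, with 400,000 infants per run. Estimates adjusted for both variables:

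| Change in mean count | 3 points, severity no effect on score | 3 points, severity affects score | 6 points, no effect | 6 points, affects score |
|---|---|---|---|---|
| 0 | 4.00 | 3.99 | 3.97 | 3.99 |
| −0.1 | 3.64 | 3.48 | 3.36 | 3.18 |
| −0.2 | 3.34 | 2.94 | 2.74 | 2.37 |
| −0.3 | 3.00 | 2.41 | 2.08 | 1.54 |
| +0.1 | 4.34 | 4.48 | 4.62 | 4.86 |
| +0.2 | 4.68 | 5.04 | 5.26 | 5.64 |

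Without the two covariates the estimate is 4.0 in every row.

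**4. If the same list were applied to morbidity outcomes.** Assumed: four morbidities with baseline risks of 40%, 8%, 10% and 8%, a shared severity factor, a conditional odds ratio of 0.70 for each, and 1,000,000 infants. Unadjusted odds ratios are 0.72, 0.70, 0.71 and 0.70. Adjusted for a count that includes the outcome, they are 1.00, 1.00, 1.01 and 0.99.

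**The case against.** The strongest reply is that the randomised question is answered by the primary analysis, which has no covariates, and that this model is secondary. That is right. A reader might infer that the trial's main result or its sample size is compromised; the documents do not support that.

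Second, bias requires an effect of treatment on the covariates, and the trial hypothesises only that morbidity will not increase. This also stands: the first row of the table shows essentially no shift. But the hypothesis is under test, so the analysis cannot assume it. Nor do the documents support a claim that benefit would be understated, because the estimate can move either way.

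Third, a few events, such as an early IVH, may precede randomisation within the consent window. True, but most of the count and most steroid use will follow it.

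Fourth, a reader might infer that morbidity outcomes are adjusted for themselves. The article does not say so. The full list is written for cognitive scores and comes after the sentence that points back, the count is undefined, the sentence is part of a brief summary, and estimands are left to a SAP that is not shown. It is a risk of one reading. Nor does that reading reach survival in the same way, since a morbidity count does not contain death; there the problem would again be adjustment for a possible mediator. The illustration shows an effect vanishing and gives no support for a reversal.

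Finally, safety is also followed through adverse-event reporting and the monitoring committee's composite outcome, for which no covariate adjustment is stated.

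**Conclusion.** The point holds for the secondary cognitive model. As written, it conditions on two variables determined mostly after randomisation, one of them a count of events of a kind the trial treats as outcomes, without saying that it targets anything other than the effect of assignment. If treatment affects either variable, the coefficient is not the total effect. The size and direction cannot be known from the documents. With the assumed inputs, a true 4-point effect is estimated at about 1.5 to 5.6, and at about 4.0 if neither variable is affected. Four points is also the difference the article calls the smallest that would change care, so shifts of this order would matter to a reader.

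The back-reference in the general methods is a definite ambiguity. Self-adjustment of morbidity outcomes is only a possible consequence of it; the move from about 0.70 to about 1.0 depends on the assumed count and risks.

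The primary analysis and the figures of 624 and 868 stand. This should be fixed, but it does not threaten the trial's main answer.

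**What to change.** Under Secondary analysis, delete postnatal steroid use and the key neonatal morbidity count. Keep the remaining covariates, measured before randomisation: site, gestational-age stratum, sex, birth weight z-score, multiple birth, antenatal steroids, socioeconomic status and parental risk index.

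If the pathway through morbidity or steroid use is of interest, put those two variables in a separate analysis labelled as exploratory mediation.

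Under Statistical methods for primary and secondary outcomes, replace the back-reference with that explicit baseline list. Do this in the SAP as well, before the in-hospital outcomes are analysed.

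The cost is wording in the protocol and SAP, and slightly less residual variance explained in the cognitive model. The sample size and data collection do not change.
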